### Sample size calculation

The sample size was calculated to detect a significant change in low back pain that could be relevant in terms of absenteeism from work [54]. Taking into account the average low back pain intensity of 5.0 ± 2.6 in the 0–10 NRS for pain observed in previous studies carried out by our research group in eldercare workers [55] and accepting an alpha error of 0.05 and a beta error of 0.20 in a bilateral contrast, 108 participants are necessary to detect a difference equal to or greater than 1 unit. The sample size has been increased by 20% due to expected dropouts. Therefore, the required sample will be 130 participants (65 in the control group and 65 in the experimental group).

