## Methods

### Study design

A parallel-assignment, multicenter randomized controlled trial will be carried out. Participants will be recruited from institutions providing eldercare services at home or in long-term facilities. In each of the institutions, and following baseline measurements, participants will be randomly assigned (1:1 ratio) through sealed opaque envelopes to either a control or experimental group by a coin-tossing sequence generation. Assessments of primary and secondary outcomes will be conducted at baseline and at 12 weeks (post-supervised phase) and 48 weeks (post-unsupervised phase) from the beginning of the intervention (Fig. 1). Outcome assessors and data analysts will be blinded to group allocation. Because of the nature of the study, blinding of the participants and the professional supervising the sessions is not possible. The study was designed, and the results will be reported according to the SPIRIT statement [30] and CONSORT guidelines for trials of nonpharmacologic treatment interventions [31].

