Some of the strengths of this study are its randomized controlled design, as well as its proper sample size calculation. In addition, methodological details have been thoroughly described, thus ensuring replicability. Besides, the unrestrictive selection criteria will allow the great majority of eldercare workers to participate, giving the study a pragmatic nature that allows it to be highly applicable to what would happen in a real work environment. Finally, the long-term effects of the intervention will be measured with an additional 48-week follow-up.

However, some limitations should be acknowledged. For example, the study might not be powered enough to assess the effects on the secondary outcomes, so it would probably be necessary to carry out new studies to establish reliable conclusions regarding those variables. In addition, compliance during the unsupervised phase of the study is self-reported. Lastly, due to the specificity of the sample in our study, the results may not be directly applicable to other professionals with high rates of musculoskeletal pain.

In conclusion, this study will assess the effectiveness of a videoconference-based therapeutic exercise program that, if successful, will allow to implement effective, scalable and affordable interventions to tackle musculoskeletal disorders in a critical population for the future of the aging societies as it is the eldercare workers.

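### The stated inputs require 108 participants per group, but 108 is used as the total for both groups, so unadjusted power for a 1-point difference is about 51%, not 80%

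*Protocol article*

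**What the plan says.** The Sample size calculation section of the protocol article takes low back pain from the group's earlier work, "average low back pain intensity of 5.0 ± 2.6 in the 0–10 NRS", as its only measure of spread. It sets the error rates by "accepting an alpha error of 0.05 and a beta error of 0.20 in a bilateral contrast" and concludes that "108 participants are necessary to detect a difference equal to or greater than 1 unit". After a 20% increase for dropout, "the required sample will be 130 participants (65 in the control group and 65 in the experimental group".

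The Study design section describes a parallel, 1:1 randomised trial. The Statistical analysis plan section analyses the intervention effect by ANCOVA with baseline as covariate, separately at 12 and 48 weeks. The sample size section mentions neither ANCOVA nor a correlation between baseline and follow-up.

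The Discussion lists among the strengths "its randomized controlled design, as well as its proper sample size calculation". Its limitations paragraph concedes possible low power for the secondary outcomes only. The Trial status section says that recruitment is open and will end once the required number is reached.

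**The concern.** An SD of 2.6 and a difference of 1 make a standardised effect of 1/2.6 = 0.385. Detecting that with 80% power takes just over 100 participants in each of two groups, so a total of 108 looks like a per-group answer used for the whole trial.

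This figure supports the primary outcome. The 1-point target was chosen as relevant to sickness absence. If power for it is near one half, a true 1-point benefit could be missed about as often as it is found, while readers would take a null result as coming from a trial with 80% power. The Discussion's warning about power would not correct them, because it excludes the primary outcome. The number also decides when enrolment stops.

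**Working it through.** **Inputs.** All are from the Sample size calculation section except the allocation, which is from Study design: SD 2.6; difference 1 NRS point; alpha 0.05, two-sided; power 1 − 0.20 = 0.80; two groups, 1:1.

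**1. The plan's own chain.** 108 × 1.2 = 129.6, rounded to 130 = 65 + 65. Before the dropout allowance this is 108/2 = 54 per group. The 108 is therefore used as a two-group total.

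**2. Required size for two independent means.**

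- Normal approximation: n per group = 2 × (1.960 + 0.842)² × 2.6² / 1² = 106.1, rounded up to 107.
- Noncentral t: 107.1, rounded up to 108. Power is 0.7997 at 107 per group and 0.803 at 108.

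So 108 is reproduced exactly, but as a per-group figure. The total is 216.

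**3. Can 108 be obtained as a total in another way?**

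- One-sided test: 84 (normal) or 85 (t) per group, 168 to 170 in total. No.
- Change scores with correlation r = 0.5: the SD of change is 2.6 × √(2 × 0.5) = 2.6, so the requirement per group is unchanged. No.
- One-sample or paired formula: (1.960 + 0.842)² × 2.6² = 53.06, rounded up to 54, and 2 × 54 = 108. The number matches, but this formula concerns change within one group, not the difference between two.

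**4. Power on the stated inputs** (two-sample t-test, 1 point, SD 2.6).

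| Analysed per group | Power for 1 point | Difference detectable at 80% |
|---|---|---|
| 52 (130 less 20%, halved) | 49% | 1.44 |
| 54 (the plan's evaluable number) | 51% | 1.41 |
| 65 (no dropout) | 59% | 1.29 |
| 108 | 80% | 1.00 |

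The 52 arises because multiplying by 1.2 does not offset a 20% loss: 130 × 0.8 = 104. With 54 per group, 80% power would need an SD of about 1.85 (normal approximation: √(54/2) / 2.802).

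**5. Credit for the planned ANCOVA.** The residual SD is 2.6 × √(1 − r²), where r is the baseline-to-follow-up correlation. The protocol gives no r, so the values below are assumptions. Power is from the noncentral t with one degree of freedom removed for the covariate.

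| r (assumed) | 54 per group | 65 per group |
|---|---|---|
| 0.3 | 55% | 63% |
| 0.5 | 63% | 71% |
| 0.6 | 70% | 78% |
| 0.7 | 79% | 86% |

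The r at which power reaches 80% is about 0.71 with 54 per group, 0.63 with 65, and 0.72 with 52.

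**The case against.** The strongest objection is that 51% belongs to an unadjusted t-test, whereas the planned analysis adjusts for baseline. The trial's real power depends on r and on how many participants are analysed. Over r of 0.3 to 0.7 and 54 to 65 per group it runs from 55% to 86%, and with no dropout an r of about 0.63 would be enough. This stands as a limit on what 51% means: it is the power on the printed inputs, not a forecast for the final analysis. It does not rescue the printed calculation, which names its inputs and gives neither a correlation nor an adjusted SD. The favourable end also needs the absence of the dropout that the protocol itself expects.

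A second objection is that the origin of 108 cannot be known, since doubling a paired calculation gives the same figure. That is true, but the conclusion does not depend on it. Whatever route was taken, 108 is what the inputs require per group, and the total is short by half.

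A third is that a journal article is condensed and a correlation may appear in a fuller document. That could alter the estimate of true power. It would not make the published inputs yield the published number.

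A fourth is that whether to enlarge the trial or restate its power is for the sponsor to decide while recruitment is open. This is fair, and the correction below leaves that choice open.

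**Conclusion.** The concern holds. The stated inputs require 108 per group, 216 in total, and the plan uses 108 as the total. On those inputs power for 1 point is 51% with 54 per group, and between 49% and 59% from 52 to 65 per group, against the stated 80%. This rests only on the printed SD, difference, alpha and allocation, and on a two-sample t-test.

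With the planned ANCOVA, the 80% claim is met at 54 per group only if r is about 0.71 or more, an assumption that the protocol does not make. The description of the calculation as a strength is unsupported as written. The error concerns the primary outcome and must be corrected.

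**What to change.** Planned enrolment can stay as it is; the statements about it need to change.

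- **Sample size calculation:** say that SD 2.6, a 1-point difference, two-sided alpha 0.05 and 80% power require 108 per group. Say that with 54 per group completing, the unadjusted power for 1 point is about 51% and the difference detectable at 80% is 1.41 points. Give the ANCOVA power for a declared range of r, for example 55% to 79% for r from 0.3 to 0.7, with the source of any r that is preferred.
- **Discussion:** remove the sample size calculation from the strengths, and extend the limitation on power to the primary outcome.
- **Interpretation:** state that a non-significant primary result will be read from its 95% confidence interval against 1 point, and not as evidence of no effect.

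The cost is wording and a less favourable stated power; no extra participants are needed. If the sponsor would rather keep the 80% claim unadjusted, the target is 216 evaluable participants, or 216/0.8 = 270 enrolled with 20% dropout.

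### The 20% dropout allowance multiplies 108 by 1.2, so 130 covers at most 16.9% loss; the step costs about 1.5 points of power, far less than the unexplained basis of 108 itself

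*Protocol article*

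**What the plan says.** All the figures are in the protocol article, Sample size calculation. The error rates come from "accepting an alpha error of 0.05 and a beta error of 0.20 in a bilateral contrast". The variability is taken from an "average low back pain intensity of 5.0 ± 2.6 in the 0–10 NRS for pain". From these the article concludes that "108 participants are necessary to detect a difference equal to or greater than 1 unit". It then says "The sample size has been increased by 20% due to expected dropouts", and that "the required sample will be 130 participants (65 in the control group and 65 in the experimental group"). Study design gives 1:1 allocation. No other section states a dropout rate or changes the allowance.

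Statistical analysis plan specifies an ANCOVA with the baseline value as covariate, run separately for 0 vs 12 weeks and 0 vs 48 weeks. Trial status says that recruitment stops once the required sample size is reached, so 130 is the number that ends enrolment. The Discussion lists among the study's strengths its randomised design "as well as its proper sample size calculation". Its only caution about power concerns the secondary outcomes.

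**The concern.** Dropouts are lost from the people randomised, not from the completers wanted at the end. An allowance for a loss fraction d therefore divides the completer target by (1 − d). Multiplying by (1 + d) always falls short. Here 108 is called necessary and 20% is tied to expected dropouts, yet 20% loss from 130 does not leave 108.

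At stake is whether the stated 80% power for a 1-unit difference survives the loss the plan appears to allow for. It also matters whether a reader can trust a paragraph that the Discussion presents as a strength. Follow-up runs to 48 weeks, 36 of them unsupervised. Intention-to-treat analysis regardless of adherence does not supply outcomes for people who are not assessed, so the number of completers matters.

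**Working it through.** **Inputs from the article:** two-sided alpha 0.05; power 0.80; SD 2.6; difference 1 NRS unit; 108 necessary; 20% increase; 130 final; 1:1 allocation. **Assumption, not in the article:** a baseline–follow-up correlation r, shown at 0.5 and 0.7.

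**1. The plan's own figure.** 108 × (1 + 0.20) = 129.6, rounded up to 130, or 65 per arm. This reproduces the stated number, so the allowance was multiplicative.

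**2. What 130 delivers at 20% loss.**
- Completers: 130 × 0.80 = 104, or 52 per arm; shortfall 108 − 104 = 4.
- Enrolment needed to keep 108: 108/(1 − 0.20) = 135. With equal arms, 54/0.80 = 67.5, so 68 per arm and 136 in total.
- Largest loss that still leaves 108: (130 − 108)/130 = 22/130 = 16.9%.

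**3. Cost of the dropout step alone.** Take the plan at its word that 108 (54 per arm) gives 80% power. By normal approximation the test statistic is then centred at 1.960 + 0.842 = 2.802. It scales with the square root of n, so at 52 per arm it is 2.802 × √(52/54) = 2.749. Power is Φ(2.749 − 1.960) = Φ(0.789) ≈ 78.5%, a loss of about 1.5 points.

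**4. Whether 108 follows from its inputs.** For two means, n per group = 2 × (2.802 × 2.6)² / 1² ≈ 106.1, so 107 per group and 214 in total. The t-test version gives 107.1, so 108 per group and 216 in total. The stated 108 matches a per-group figure, not a total.

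For 54 per arm to give 80% power, the SD in the analysis would have to be √(54/2)/2.802 ≈ 1.85. Under ANCOVA the effective SD is 2.6 × √(1 − r²), so r = √(1 − (1.85/2.6)²) ≈ 0.70. The article states no such correlation. By the same normal formula, r = 0.5 would need 160 in total and r = 0.6 would need 136.

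**5. Separating the two effects.** Two-sided t-test, difference 1, SD 2.6 × √(1 − r²):

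| Completers per arm | Unadjusted power | r = 0.5 | r = 0.7 | Unadjusted difference detectable at 80% power |
|---|---|---|---|---|
| 54 (all 108) | 50.8% | 62.8% | 79.2% | 1.41 |
| 52 (130 less 20%) | 49.3% | 61.2% | 77.6% | 1.44 |

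Reading down a column, the dropout step costs about 1.5 points of power and 0.03 units. The rest of the gap to 80% is already there at 54 per arm. With no dropout at all (65 per arm), unadjusted power is still only about 59%.

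**The case against.** The strongest reply is that the article never states a 20% dropout rate. It states a 20% increase, and that increase is computed correctly. On the literal wording, 130 covers losses up to 16.9% and nothing contradicts anything. This stands in part: a 20% loss rate is an inference. But the sentence ties the 20% to expected dropouts and no other rate appears, so most readers will take it that the trial tolerates 20% loss. If the expected rate is 16.9% or lower, one sentence saying so settles the matter.

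The second reply is that the effect is trivial: four participants and about 1.5 points of power, from a shortcut in common use. As to size, that is right, and nothing larger should be claimed for the dropout step.

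A reader who sees 49% power at 52 per arm might infer that the dropout arithmetic brings power down from 80% to 49%. The figures do not support that. Unadjusted power is already about 51% with all 108 completers, so nearly the whole gap comes from giving as a total a number that the stated inputs require per group. Nor does 135 or 136 rescue the design: it protects the 108 target, but 80% power follows only if the basis of 108 is also justified.

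**Conclusion.** The point holds in a limited form. On the natural reading that 20% is the expected dropout rate, 130 randomised gives 104 completers against the 108 called necessary, and the real tolerance is 16.9%. Taken alone this lowers power from 80% to about 78.5%, assuming 108 truly gives 80%.

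That assumption is the weaker part of the paragraph. With SD 2.6 and a 1-unit difference, about 108 are needed per group. A total of 108 reaches 80% only under an ANCOVA with a baseline correlation of about 0.7, which the article does not state. The two issues are separate and add together; the second is by far the larger. It would go too far to say that the calculation is certainly underpowered, because the planned analysis does adjust for baseline and the correlation could be that high. What can be said is that the text does not show it.

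**What to change.** No additional enrolment is asked for. In Sample size calculation:

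- State the assumed dropout rate. If it is 20%, say that 130 randomised gives 104 expected completers (52 per arm), and that 130 retains 108 only if loss is at most 16.9%. For reference, 108 completers at 20% loss would need 135, or 136 with equal arms.
- Restate the power, or the difference detectable with 80% power, for 52 completers per arm under the planned ANCOVA. Give the assumed baseline–follow-up correlation and its source.
- Say plainly that the main shortfall comes from the basis of 108, and that only about 1.5 points come from the dropout step.

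In the Discussion, qualify the listing of the sample size calculation as a strength so that it agrees with the restated figures, and extend the caution about power to the primary outcome if the restated power is below 80%.

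The cost is a few sentences, and a stated power less favourable than the present 80% unless a correlation slightly above 0.7 can be supported.

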### Statistical analysis plan

IBM SPSS Statistics 27 statistical software package (SPSS, Inc., Chicago, IL) will be used for data analysis. Normality of distribution will be checked using the Kolmogorov‒Smirnov test, and non-normally distributed variables will be square-root transformed for statistical analysis. Continuous and categorical data will be reported as mean (standard deviation) and frequency (percentage), respectively. The primary analysis will be based on intention-to-treat, including data from all participants regardless of adherence to the intervention. Additionally, a per-protocol analysis will be performed, including only data from participants with ≥ 50% adherence. Finally, a post-hoc subgroup analysis will be performed to assess the effects of the intervention on low back pain outcomes separately in participants with (≥ 1 in average 0–10 NRS) and without (< 1 in average 0–10 NRS) low back pain at baseline. Between-group comparisons at baseline will be performed with the independent samples T and Chi-squared tests for continuous and categorical variables, respectively. For continuous variables, intervention effects will be analyzed with a group-by-time ANCOVA including baseline measurements as covariates. This ANCOVA will be performed separately to assess intervention effects in two time periods: 0 vs 12 weeks and 0 vs 48 weeks. Within-group changes in each time period will be performed with the paired samples T test. Effect size will be estimated by partial eta squared (η^2^). Values for η^2^of 0.02, 0.13, and 0.26 will be considered small, medium and large, respectively [56]. For categorical variables, intervention effects will be analyzed with McNemar’s test. The level of statistical significance will be set at *p* < 0.05.

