#### Primary outcome

The primary outcome will be average pain intensity in the low back during the last 7 days, measured by the 0–10 Numerical Rating Scale (NRS) [41] ranging from 0 (complete absence of pain) to 10 (worst imaginable pain) (Table 2).

**Table 2 Tab2:** Detailed description of the outcome measures that will be assessed in the trial

Questionnaire/Test	Functions/Parameters	Description
**Musculoskeletal pain**^**a**^		
0–10 Numerical Rating Scale (NRS) for pain [41]	Pain intensity (average and worst)	Intensity during last 7 days (0–10)
Ad hoc question	Pain frequency	Days in pain during last 7 days (0–7)
Ad hoc question	Pain interference	Days in which pain negatively interferes with work during the last 7 days (0–7)
Ad hoc question	Pain medication consumption	Days of analgesic medication consumption during last 7 days (0–7)

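### The normality-test-and-square-root rule does not exempt the primary NRS outcome, so it can move the primary test off the scale of the 1-point target

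*Protocol article*

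**What the plan says.** The Statistical analysis plan section of the protocol article states: "Normality of distribution will be checked using the Kolmogorov‒Smirnov test". It then gives the consequence of a failed test: "non-normally distributed variables will be square-root transformed for statistical analysis". The rule covers every variable. It does not say:

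- which form of the test is meant (with or without the Lilliefors correction for an estimated mean and SD);
- whether arms are pooled or tested separately;
- what happens if baseline and follow-up scores get different verdicts.

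Intervention effects on continuous outcomes come from a baseline-adjusted ANCOVA, run separately for 12 and 48 weeks. On the size of the effect, the section says: "Effect size will be estimated by partial eta squared". It also says that continuous data will be reported as means with standard deviations.

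The Primary outcome section defines the endpoint on the raw scale: "The primary outcome will be average pain intensity in the low back during the last 7 days, measured by the 0–10 Numerical Rating Scale". The Sample size calculation is on that scale too: "108 participants are necessary to detect a difference equal to or greater than 1 unit".

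**The concern.** The trial's target is a constant difference of 1 NRS point, chosen for its relevance to absenteeism. On the square-root scale a 1-point fall has no constant size, so a transformed ANCOVA tests a different quantity, and the data decide which of the two is tested.

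The trigger is also poorly matched to its purpose. ANCOVA needs approximately normal residuals, whereas the rule acts on the distribution of the variable itself. A Kolmogorov-Smirnov test can reject merely because scores are whole numbers, a feature that a square root cannot remove. A square root reduces right skew only; applied to a symmetric or left-skewed score it adds left skew.

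At stake are the interpretability of the primary result against its own target, some power, and in a minority of trials the significance verdict.

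**Working it through.** **Inputs from the protocol.** Mean and SD: "average low back pain intensity of 5.0 ± 2.6 in the 0–10 NRS for pain". Error rates: "accepting an alpha error of 0.05 and a beta error of 0.20 in a bilateral contrast". Target: 1 NRS unit. Evaluable total 108, taken here as 54 per arm; 130 after the dropout allowance (65 per arm).

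**Assumptions.** Whole-number answers, a normal latent score limited to 0–10, and a baseline–follow-up correlation r of 0.5 (0.7 as an alternative). The protocol gives none of these.

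**The plan's own figure.** For two independent groups, n per arm = 2(1.960 + 0.842)² × 2.6² / 1² = 106.1, so 107 per arm and 214 in total. The stated 108 does not follow from this. It appears as 2 × 54 from the one-sample formula (7.849 × 6.76 = 53.06, rounded up to 54), or from an ANCOVA with an unstated r of about 0.70. The final step does follow: 108 × 1.2 = 129.6, hence 130. This is a separate matter. It is shown because 54 per arm is used below, and because the calculation is plainly in raw NRS units.

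**Step 1: how often the rule fires.** Share of 20,000 simulated samples with normality rejected at 0.05, for scores from N(5.0, 2.6) rounded and limited to 0–10:

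| n tested | Lilliefors | Uncorrected |
|---|---|---|
| 54 (one arm) | 58% | 2% |
| 65 (one arm) | 71% | 3% |
| 108 (pooled) | 98% | 14% |
| 130 (pooled) | 99.8% | 24% |

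Across independent runs the pooled figures lie within about 95–100% and 13–26%. Without rounding, the Lilliefors test rejects in 4–5%, so under that variant rounding is what trips it. If answers in half points are allowed, Lilliefors rejects in 16–45% over the four sample sizes.

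Pain-free workers are eligible, and the plan has a subgroup with baseline NRS below 1, so zeros are expected. As an illustration, let 20% score 0 and let the other 80% follow the distribution above. Rejection rises to 86–100% (Lilliefors) or 15–89% (uncorrected). The overall mean is then about 0.8 × 5.0 = 4.0, so this is not the planning population. It shows direction only.

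**Step 2: whether the square root cures it.** The symmetric score goes from skewness 0.00 to −1.15. At n = 130, normality is still rejected after transformation in 100% (Lilliefors) or 96% (uncorrected). Assumed left-skewed shapes get worse: a 0–10 score from −0.56 to −0.93, a 0–100 score from −0.60 to −0.94.

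**Step 3: what is then tested.** A 1-point fall on the square-root scale:

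- from 9 to 8: √9 − √8 = 0.17
- from 5 to 4: √5 − √4 = 0.24
- from 1 to 0: √1 − √0 = 1.00

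**Step 4: effect on the primary test.** Simulated ANCOVA, 54 per arm, 1-point shift:

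| Assumed r | Power, raw | Power, square root | Verdicts differ |
|---|---|---|---|
| 0.5 | about 61% | about 57% | about 12% |
| 0.7 | 76% | 70% | 11% |

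The last column compares always analysing raw scores with always analysing square roots. With no true effect, applying the rule as written gives a type I error of 5.1% (Lilliefors) or 5.0% (uncorrected).

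**The case against.** The strongest defence has four parts.

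1. **The rule may seldom fire.** The article names only the Kolmogorov-Smirnov test. With uncorrected critical values it fires on a rounded, otherwise normal score in 2–24% of samples, and its verdict then differs from a raw ANCOVA in only about 1.5% of trials. This stands. A reader might infer that whole-number scoring alone will almost certainly trigger the transformation. That needs the Lilliefors correction, whole-number answers and pooled arms, none of which the protocol states.
2. **Raw results will still be seen.** Means and SDs are to be reported, so it would be too strong to say that the result could not be set against 1 point at all. This also stands, but those means are not the tested contrast, and no adjusted difference in NRS points is named.
3. **The rule is mechanical and prespecified.** It does not inflate type I error, and the power loss is a few percentage points. This stands and limits the severity.
4. **Harm to secondary outcomes is hypothetical.** The documents give no distribution for work ability, happiness or health state, so one cannot say that they will be left-skewed. What does stand is that a square root worsens any outcome that is.

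An article may leave detail to a fuller plan. Here, though, the rule itself is stated, without exception, so the point does not rest on an omission.

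**Conclusion.** The concern holds in a limited form, with moderate confidence. The protocol fixes a data-driven rule that can replace the planned comparison of mean NRS with one of mean square-root pain, and it names no effect measure that returns an adjusted difference in NRS points. This conclusion does not depend on the test variant. The frequency does: from near-certain to about one sample in seven (n = 108) or four (n = 130) when arms are pooled, and lower still if arms are tested separately.

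Where the rule fires, the cost is about 4 to 6 percentage points of power and a changed significance verdict in about 11–12% of trials, given 54 per arm and an assumed r of 0.5 to 0.7. The documents do not support a claim of false-positive inflation. The defect is one of interpretability and efficiency, and it is worth correcting because correction is nearly free.

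**What to change.** - Remove the test-and-transform rule for the primary outcome.
- Analyse the NRS untransformed by baseline-adjusted ANCOVA at 12 and 48 weeks. Report the adjusted mean difference in NRS points with its 95% confidence interval, read against the 1-point target. Partial eta squared may stay as a supplement.
- Check the model residuals rather than the raw variable. Keep any transformed, robust or bootstrap analysis as a prespecified sensitivity analysis.
- State that a square root will not be applied to left-skewed secondary outcomes.

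The cost is a change of analysis wording. No data collection, visit or sample size changes. The Trial status section says that recruitment is still open, so the change can be recorded before outcome data are analysed.

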### Inclusion and exclusion criteria

Subjects will be considered eligible for the study if they meet all the following criteria: (a) are formal eldercare workers from eldercare institutions, (b) are ≥ 18 years of age, (c) have ≥ 3 months of experience in the profession, and (d) have an employment contract until at least the date of study completion. Participants will be excluded if (a) they are pregnant or (b) their participation is considered contraindicated according to the American College of Sports Medicine’s exercise preparticipation health screening guidelines [32].

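### The planned split by baseline low back pain names no interaction test and is mislabelled post hoc, so two separate p-values could be read as a difference in effect

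*Protocol article*

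**What the plan says.** The protocol article, Statistical analysis plan, lists three analyses. The intention-to-treat analysis is primary and a per-protocol analysis follows. Last, "a post-hoc subgroup analysis will be performed to assess the effects of the intervention on low back pain outcomes separately in participants with" pain (average NRS of at least 1) and those "without (< 1 in average 0–10 NRS) low back pain at baseline".

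For continuous outcomes, "intervention effects will be analyzed with a group-by-time ANCOVA including baseline measurements as covariates". This is run once for each of "two time periods: 0 vs 12 weeks and 0 vs 48 weeks". Group-by-time is the only interaction named. One threshold serves every test: "The level of statistical significance will be set at" p < 0.05.

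Under Inclusion and exclusion criteria, "Subjects will be considered eligible for the study if they meet all the following criteria"; the criteria that follow concern occupation, age, experience and contract. Pain is neither required nor excluded, so both strata can be enrolled. The Trial status section says that recruitment is still active.

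**The concern.** There are three separate weaknesses.

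- **Method.** Whether the effect depends on baseline pain is a question about the difference between two effects. Estimating and testing each stratum on its own does not answer it. Each stratum has far fewer participants than the trial, and the two are unlikely to be equal in size, so one significant and one non-significant result can easily arise when the effect is the same.
- **Scale floor.** The Primary outcome section anchors the NRS at 0 for no pain. A participant below 1 has almost no room to improve, so the two strata are not asking the same thing of the scale.
- **Label.** The variable, the cut-off and the outcomes are all written down while recruitment continues. Calling the analysis *post hoc* misstates its status.

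What is at stake is a secondary message: that the programme works in workers with pain and not in those without, resting on two p-values rather than on a comparison of effects.

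**Working it through.** **Inputs from the documents** (Sample size calculation): "average low back pain intensity of 5.0 ± 2.6 in the 0–10 NRS", a target difference of 1 unit, "accepting an alpha error of 0.05 and a beta error of 0.20 in a bilateral contrast", 108 evaluable participants, 130 after the dropout allowance, 1:1 allocation. The documents give no figure for the subgroup analysis itself.

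**The plan's own figure.** With SD 2.6, n per arm = 2 × (1.96 + 0.8416)² × 2.6² / 1² = 106.1, rounded up to 107, or 214 in total. The stated total of 108 does not follow from the stated inputs. That is a separate matter, but it bears on the SD used here. With 54 per arm, 80% power requires SD = 1 / (2.8016 × √(2/54)) = 1.85. Under ANCOVA this corresponds to a baseline correlation of √(1 − (1.85/2.6)²) ≈ 0.70, which the article does not state. I therefore use SD 2.6 and SD 1.85 as the two ends of a range.

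**Assumptions:** the same true effect of 1 unit in both strata; a share with pain of 50% to 90%; the same SD in both strata; 108 or 130 participants analysed.

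**Formulas,** with a and b participants per arm in the pain and pain-free strata:
- power in a stratum = Φ(1 / (SD√(2/n)) − 1.96), where n is a or b
- P(exactly one significant) = pA(1 − pB) + pB(1 − pA)
- SE of the interaction = SD√(2/a + 2/b); its power for a 1-unit difference = Φ(1/SE − 1.96); the difference detectable with 80% power = 2.8016 × SE

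**Worked case:** N = 108, SD 2.6, 80% with pain, so a = 43.2 and b = 10.8.
- pA = Φ(1/0.559 − 1.96) = 0.432
- pB = Φ(1/1.119 − 1.96) = 0.143
- exactly one significant: 0.432 × 0.857 + 0.143 × 0.568 = 0.451
- interaction SE = √(0.559² + 1.119²) = 1.251; power 0.123; detectable difference 3.50 units

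| N | SD | Pain share | Power, pain | Power, pain-free | Exactly one significant | Interaction power, 1 unit | Detectable difference |
|---|---|---|---|---|---|---|---|
| 108 | 2.6 | 50% | 0.292 | 0.292 | 0.414 | 0.168 | 2.80 |
| 108 | 2.6 | 80% | 0.432 | 0.143 | 0.451 | 0.123 | 3.50 |
| 108 | 2.6 | 90% | 0.474 | 0.092 | 0.479 | 0.087 | 4.67 |
| 108 | 1.85 | 50% | 0.508 | 0.508 | 0.500 | 0.288 | 2.00 |
| 108 | 1.85 | 80% | 0.707 | 0.240 | 0.608 | 0.201 | 2.50 |
| 108 | 1.85 | 90% | 0.757 | 0.141 | 0.685 | 0.131 | 3.33 |
| 130 | 2.6 | 50% | 0.341 | 0.341 | 0.449 | 0.194 | 2.56 |
| 130 | 2.6 | 90% | 0.548 | 0.103 | 0.538 | 0.096 | 4.26 |
| 130 | 1.85 | 50% | 0.585 | 0.585 | 0.486 | 0.336 | 1.82 |
| 130 | 1.85 | 90% | 0.830 | 0.162 | 0.724 | 0.150 | 3.04 |

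Discordant significance under an identical effect runs from 0.414 to 0.724. Even an equal split gives 0.414 to 0.500, so low power is the main cause. Imbalance adds to it and makes the pain stratum the likelier one to be significant.

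**Can the pattern tell the two situations apart?** In the worked case, set the true effect in the pain-free stratum to zero, so that its chance of significance is 0.05. Then P(exactly one significant) = 0.432 × 0.95 + 0.05 × 0.568 = 0.439, against 0.451 when the effects are equal. The pattern of p-values says almost nothing about whether the effect differs.

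**Floor.** If the NRS is answered in whole numbers (an assumption), everyone below 1 scores exactly 0. The baseline covariate is then constant in that stratum and adjusts for nothing, and a within-group change there can only be zero or a worsening.

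**The case against.** A reader might infer more than the documents support, on four counts.

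- *That differing p-values will be taken as a differential effect.* The plan says only that effects will be assessed in each stratum. It does not say that the results will be compared or what will be concluded. That they could be misread is as far as the text goes.
- *That the label causes the misreading.* It does not; if anything, *post hoc* lowers the weight a reader gives the result. It is a separate error about status.
- *That this analysis will decide who benefits.* Nothing says so. It is listed last, after the intention-to-treat and per-protocol analyses.
- *That a null result in the pain-free stratum is forced by arithmetic.* ANCOVA compares arms at follow-up, so a benefit can show as less new pain than in controls. The Discussion mentions prevention as well as treatment, so reporting the strata apart is reasonable in itself.

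The common-effect calculation is also open to challenge. It places a 1-point effect, and at SD 1.85 a useful covariate, in a stratum at the floor. A real difference on the NRS is partly built in there. This stands, so the figures are an illustration and not a forecast.

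Finally, a fuller analysis plan may contain an interaction test. That would settle the missing comparison. It would not correct the label, and the method this article does state is separate assessment by stratum.

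**Conclusion.** The point holds as a defect in a secondary analysis. The article fixes separate assessment in two baseline strata, names no treatment-by-subgroup test, and labels a pre-planned analysis *post hoc*. If the two p-values were compared, they could mislead: under a common 1-point effect, a pain share of 50% to 90% and an SD of 1.85 to 2.6, exactly one stratum is significant about 41% to 72% of the time. The range rests on those assumptions because the documents give neither the split nor the baseline correlation. The label error and the floor effect do not depend on the calculation. The primary intention-to-treat result is not touched.

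**What to change.** Amend the sentence in the Statistical analysis plan so that it:

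- calls the analysis pre-specified and exploratory;
- adds a group-by-baseline-pain interaction (NRS at least 1 versus below 1) to the ANCOVA fitted on all participants;
- reports the interaction and both stratum effects with 95% CIs from that model;
- states that no differential-effect claim will be made from stratum p-values alone;
- describes, in the pain-free stratum, the proportion developing low back pain in each arm.

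The cost is a few lines of text and one model term, with no new data.

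The downside should be stated with it. With 108 participants the interaction test has about 9% to 29% power for a 1-unit difference between strata (10% to 34% if all 130 are analysed), and it partly reflects the floor. A non-significant interaction is therefore not evidence of equal effects, and the confidence interval should carry the interpretation.
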